Consequently, the presence of CU traits in children with DBD is indicated by the specifier “with limited prosocial emotions” (LPE) in the ICD-11 and DSM-5 (American Psychiatric Association, 2013; Frick et al., 2014). In case of a patient diagnosed with DBD, a specific LPE may be assigned if two CU traits—for example, lack of remorse and guilt, and shallow or deficient affection—persist for longer than one year. Approximately half the children with DBD exhibit elevated levels of CU traits (Kahn et al., 2012; Pisano et al., 2017). In analyses of risk factors for the development of CU traits, research has identified associations between parental characteristics (i.e., low parental warmth, harsh parenting, and parental psychopathology) and an increased likelihood of CU traits in their offspring (Frick & Viding, 2009; Waller et al., 2015, 2017; Wright et al., 2018). Children from families of low socioeconomic status and those from parents with adverse childhood experiences have been linked to higher levels of CU traits, while parental warmth in parenting has been identified as a protective factor (Hyde et al., 2016; Kohlhoff et al., 2020; Pueyo et al., 2022; Tomlinson et al., 2022; Waller et al., 2015).

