### 1.3. Working Hypotheses

**Construct Validity of CAPE and LPE**

*Interrater reliability and prevalence*

1.The CAPE interviews are expected to demonstrate moderate to very good interrater reliability.2.It is expected that approximately 50% of children diagnosed with DBD will also exhibit LPE.

*Convergent validity*

3.CAPE will be statistically significantly positively correlated with CU traits, DBD, (proactive) aggressive behavior, and parental strictness.

*Divergent validity*

4.CAPE will be statistically significantly negatively correlated with social competence, empathy, emotion recognition, and parental warmth.

*Incremental validity*

5.The CAPE Interview will demonstrate greater predictive validity than the ICU for DBD, social competence, (proactive) aggressive behavior, empathy, and emotion recognition.

*Group comparison of the specifier “with limited prosocial emotions”*

6.Children with an LPE will differ significantly and positively in CU trait expression, DBD, and (proactive) aggression compared to children without an LPE.7.Children with an LPE will differ significantly and negatively in social competence, empathy, emotion recognition, and parental warmth from children without an LPE.

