### 2.3. Inclusion and Exclusion Criteria

Children and adolescents between the ages of 8 and 18 years who exhibit aggressive behavior symptoms above the cut-off (FBB-SSV; (Döpfner et al., 2017): total score ≥ Stanine 7) and who have been diagnosed with DBD (ICD-10: F90.1, F91, F92) will be included. Children and adolescents with acute psychotic symptoms, reduced intelligence (IQ ≤ 70), and a limited understanding of the German language (below C1) will be excluded.

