### 2.4. Sample Size Calculation

In line with earlier findings (Colins et al., 2020; Goetz et al., 2024; Hawes et al., 2020; Molinuevo et al., 2020; Neo et al., 2023), we expect medium-to-large effect sizes for research question one when examining and comparing children with and without LPE across relevant convergent/divergent constructs (DBD and social competence, reactive/proactive aggressive behavior, emotion recognition, and empathy). Based on two groups (LPE, yes/no) in an analysis of covariance (ANCOVA), we can estimate, using G*Power 3.1 (effect size = 0.50, α = 0.05, 1−β = 0.95), that a total sample size of 55 would yield statistically significant results. We expect small-to-medium effect sizes when examining LPE correlations with relevant convergent/divergent constructs. Based on calculations (effect size = 0.40, α = 0.05, 1−β = 0.95), we can assume that a sample size of 63 patients would yield statistically significant results. In this context, moderate effects are also assumed when calculating incremental validity via hierarchical regression (effect size = 0.15, α = 0.05, 1−β = 0.95; number of tested predictors: 2; total number of predictors: 7), yielding an *N* of 83.

For research question two, children and adolescents with elevated CU traits will be separated into two groups based on whether they have primary or secondary CU traits, depending on at least two interpersonal potential traumatic events and high anxiety scores. Groups will be compared in levels of anxiety, depression scores, emotion recognition, empathy, DBD, and social competence, and reactive/proactive aggressive behavior (Bennett & Kerig, 2014; Craig et al., 2021; Craig & Moretti, 2019; Dadds et al., 2018; Kahn et al., 2013; Kimonis et al., 2012, 2013; Mozley et al., 2018; Robertson et al., 2023; Vasileva et al., 2019). According to Kimonis and colleagues (Kimonis et al., 2012, 2013), medium-to-high effect sizes are expected (Cohen’s *d* = 0.41–0.96). Kahn and colleagues (Kahn et al., 2012, 2013) reported small-to-medium effect sizes. Hence, we require an *N* of 84 (ANCOVA; G*Power: effect size = 0.40, α = 0.05, 1−β = 0.95) to estimate the required sample size. To adequately address the research question, an *N* of 84 participants is required. Given a 20% attrition rate, this would correspond to 101.

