**For research question 2:**

*Defining groups*

Patients with ‘highly descriptive’ in at least one CU Trait on the CAPE interview will be separated into two groups (primary or secondary CU traits), theory-informed by the experience of two interpersonal potentially traumatic events (≥2 = secondary CU traits) and by anxiety scores (T ≥ 70 = secondary CU traits). This approach requires that the SPJ assessment include at least one CU characteristic, thereby ensuring that the exploratory subgrouping is limited to patients who exhibit clinically relevant CU-related characteristics. It is imperative to acknowledge that this exploratory classification does not aspire to represent or supersede a formal LPE classification. We concur with Cecil et al. (2018) that data-driven methodologies, such as cluster analysis, are not feasible in a clinical context, where decisions are made according to cutoff points. Moreover, previous analyses have demonstrated that trauma allows for a distinction between primary and secondary CU traits (Cecil et al., 2018; Kimonis et al., 2012), and there is also evidence that anxiety effectively differentiates between the two forms (Todorov et al., 2025). Consequently, we adhere to the recommendations set forth by Craig et al. (2021) and undertake a comprehensive assessment of potentially traumatic experiences and anxiety levels. In this study, a cutoff of two potentially traumatic experiences will be used to account for severity and to model repeated interpersonal trauma (Karpman, 1941; Kimonis et al., 2012; Pueyo et al., 2022).

*Group comparison*

ANCOVA models assessing group differences between primary and secondary CU trait groups across relevant constructs (CU traits, emotion recognition, reactive aggressive behavior, depression, attention problems, anxiety, parental warmth/strictness, and DBD) will be conducted. We will control for age, study site (waiting list, outpatient, daycare, or inpatient), and sex in the ANCOVA models.

*Effect size and statistical assumption*

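### The N of 84 for the primary-versus-secondary comparison is not inflated for the share of children who qualify for it, so the stated 95% power is not delivered

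*Protocol article*

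**What the plan says.** Section 2.4 sizes research question 2 separately from research question 1. It states that "children and adolescents with elevated CU traits will be separated into two groups based on whether they have primary or secondary CU traits", takes "effect size = 0.40, α = 0.05, 1−β = 0.95" for a two-group ANCOVA, and arrives at 84. The section closes on "84 participants is required. Given a 20% attrition rate, this would correspond to 101". No other overall target appears in the article.

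The analysis set is defined in section 2.6 under research question 2: patients rated 'highly descriptive' "in at least one CU Trait on the CAPE interview will be separated into two groups", by trauma count and anxiety score. Section 2.5 assigns LPE only when two traits have that rating.

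Entry to the study is wider. Section 2.3 admits children above an aggression cut-off "who have been diagnosed with DBD (ICD-10: F90.1, F91, F92) will be included", with no CU-trait criterion. Research question 1 also needs children without LPE in the same sample.

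On how many will have the traits, the Introduction says "Approximately half the children with DBD exhibit elevated levels of CU traits", and the working hypotheses state "It is expected that approximately 50% of children diagnosed with DBD will also exhibit LPE". Section 1.4 cites LPE prevalences of 21.6% in outpatients and 60% in a detention centre.

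**The concern.** The calculation returns the number of children needed across the primary and secondary groups together. The plan then uses that number as its overall target, although the recruited sample also contains children who will be in neither group. Unless practically every child with DBD has at least one 'highly descriptive' trait, the comparison will be smaller than 84.

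At stake is how the research question 2 results are read. Section 1.3 states directional hypotheses for this comparison, and section 1.4 already offers a substantive explanation should parental strictness not differ. A reader who trusts the 95% figure would take a non-significant result as fair evidence against a large difference, when the comparison may have had materially less power.

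**Working it through.** **Inputs from the article.** f = 0.40, α = 0.05, power 0.95, two groups (section 2.4). Covariates age, sex and setting with four categories (section 2.6), hence 1 + 1 + 3 = 5 df. Targets 84 and 101 (section 2.4). LPE expected in about 50% (section 1.3).

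**Assumptions.** The share with at least one 'highly descriptive' trait is not given; 50–70% is used. Every child with LPE meets the one-trait rule, so an LPE share of 50% makes 50% the floor. The primary:secondary split is not given either; 1:1 is the best case.

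**Formula.** The F test has 1 and N − 2 − 5 df, with noncentrality λ = d² · N · p(1 − p), where p is the share in one group. With equal groups d = 2f = 0.80 and λ = f² · N.

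**Step 1: reproduce the plan's figure.** N = 84: λ = 0.16 × 84 = 13.44, df 1 and 77, power 0.952. N = 83 gives 0.949. So 84 is correct as the total across the two groups. The attrition step is 84 × 1.20 = 100.8, rounded to 101.

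**Step 2: apply the qualifying share (f = 0.40, 1:1 split).**

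| Share qualifying | n of 84 | Power | n of 101 (no attrition) | Power |
|---|---|---|---|---|
| 50% | 42 | 0.71 | 50 | 0.79 |
| 60% | 50 | 0.79 | 61 | 0.87 |
| 70% | 59 | 0.85 | 71 | 0.91 |
| 80% | 67 | 0.90 | 81 | 0.94 |

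For example, n = 42 gives λ = 0.16 × 42 = 6.72 with 35 residual df, and power 0.71.

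**Step 3: what 95% would require.** All 84 would have to qualify, or 84/101 = 83% of those recruited with no attrition, and in both cases the groups would have to be equal. To obtain 84 qualifying children, the analysable sample would need to be 84/0.70 = 120 to 84/0.50 = 168.

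**Step 4: unequal groups.** With d held at 0.80 and an assumed 25:75 split, p(1 − p) = 0.1875. Then n = 42 gives λ = 0.64 × 42 × 0.1875 = 5.04 and power 0.59; n = 59 gives λ = 7.08 and power 0.74. This fixes d, not f: at 25:75, d = 0.80 corresponds to f = 0.80 × √0.1875 = 0.35.

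**Step 5: detectable difference.** At 80% power and 1:1, the minimum detectable d is about 0.89 for n = 42 and 0.74 for n = 59. Section 2.4 cites d = 0.41–0.96 for such comparisons.

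**The case against.** Several points on the other side are sound.

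- *The article never says that 84 is the whole DBD sample.* The sentence closes the paragraph on research question 2 and could be read as that question's own requirement. The whole-sample reading rests on 84/101 being the only target and on eligibility having no CU criterion. But if 84 was meant as a subset target, the larger recruitment it implies is missing, so the text needs correcting either way.
- *A reader might infer that only about half of the children will enter the comparison.* The documents do not support that as the expected value. The 50% expectation is for LPE, which needs two 'highly descriptive' traits; one suffices here, so half is the floor under the plan's own expectation. The Introduction's figure of about half for elevated CU traits is not tied to this rule.
- *A reader might take the 21.6% outpatient prevalence as the expected share.* That figure is for LPE in one setting. This study also recruits inpatients and day-clinic patients and requires an aggression score above a cut-off, and the same section gives 60% in detention.
- *Losses may be below 20%.* Data come from a single appointment and completion requires all entries, so the 101-based column is a fair upper range.
- *The 25:75 split has no source in the article.* It is an illustration only.
- *Research question 2 is exploratory*, and the plan commits to reporting η². This lowers the consequence and leaves research question 1 untouched. It does not rescue a stated power of 95%: even 80% qualifying gives 0.90 to 0.94 with equal groups.

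**Conclusion.** The point stands as a mismatch between the sample-size figure and the analysis set. It is not an arithmetic error, since 84 is computed correctly. On an assumed qualifying share of 50–70% and a 1:1 split, power at the plan's f = 0.40 is about 0.71–0.85 if 84 are analysable and about 0.79–0.91 if all 101 are. Unequal groups at a fixed d would take it lower. The exact shortfall cannot be known because the plan gives neither the share nor the split, but a shortfall exists over the whole range considered. The statement should be corrected, at moderate priority: the aim is exploratory and no conclusion of research question 1 depends on it.

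**What to change.** In sections 2.4 and 2.6:

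- State that the analysis set for research question 2 is the subset with at least one 'highly descriptive' CAPE trait, and give its expected size and expected primary:secondary split with the assumptions behind them.
- Replace the 95% power claim with the achieved power for that size, or with the minimum detectable d (about 0.89 at n = 42 and 0.74 at n = 59, for 80% power and equal groups).
- Justify the total N by research question 1, where the plan's largest stated figure is the regression N of 83. Recheck that figure before it takes on this role: with the printed inputs (effect size 0.15 read as f², 2 tested of 7 predictors, power 0.95), the noncentral F calculation gives 107, and 83 gives power of about 0.88.

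Presenting the comparison as estimation, with group differences and 95% confidence intervals, would suit its exploratory status but is optional. The correction to research question 2 leaves recruitment unchanged; its cost is rewording and a less favourable stated power for an exploratory aim.

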### 2.5. Outcomes

**Clinical Assessment of Prosocial Emotions (CAPE)**

The *Clinical Assessment of Prosocial Emotions* 1.1 (CAPE 1.1 (Frick, 2013)) is a semi-structured interview developed for clinicians to assess CU traits according to DSM-5 criteria in children and adolescents diagnosed with DBD: (a) lack of remorse or guilt, (b) callousness-lack of empathy, (c) unconcerned about performance, and (d) shallow or deficient affect. The interview can be given to the child, parents, teachers, or other caregivers for an SPJ for LPE. In the study at hand, the primary caregiver will be interviewed by a trained and licensed children and adolescent psychotherapist or a trained physician from the Child and Adolescent Mental Health team. We ensure that all CAPE assessments are conducted with legal authorization to perform clinical assessments and with at least three years of experience conducting and evaluating clinical interviews with children and adolescents. These professionals were trained in psychopathology, child development, clinical interviewing, ethical standards, the research literature on CU traits, and the administration and scoring procedures of the CAPE. They are also continuously supervised by the study directors and can ask questions. The interview was translated into German using the TRAPD method (translate, review, adjudication, pretest, documentation) (Curtarelli & van Houten, 2018). During the interview, primary caregivers are asked three yes/no stem questions for each CU trait. In case of a yes response, the interviewer will ask for examples of everyday situations persistent over different settings, (e.g., Does ____ show his/her/their feelings and emotions openly to others? Please give some examples of this), the monthly frequency of the specific behavior, and for how long the symptom has lasted. After the interview, each CU trait is rated by the clinician as ‘not descriptive or mildly descriptive’ (0), ‘moderately descriptive’ (1), or ‘highly descriptive’ (2). If there are two CU traits rated as ‘highly descriptive’, LPE diagnosis is assigned. The CAPE 1.1 assessments in this study were intentionally conducted without using additional sources of information (e.g., files), even though guidelines recommend that interview data should normally be combined with such information (Frick, 2013). In accordance with the methodology by Hawes et al. (2020), the SPJ is administered following the interview with the primary caregiver. This approach is employed to ascertain the interrater reliability of the interview. The necessity for this approach is predicated on the requirement for standardized implementation across multiple study sites.

Furthermore, it reduces the burden on participants and the organizational workload whilst also avoiding overlap in criteria with the child-report questionnaires. For data analysis, the dimensional and dichotomous (LPE yes/no) score will be used. Furthermore, the second, double-blind coder for interrater reliability will be thoroughly prepared to focus on CU traits and their specific characteristics. The secondary coder will have undergone training with one of the original assessors and completed at least two sessions with that assessor before coding CAPEs herself.

Primary caregiver- and child-rated

**CU Traits**: The *Inventory of Callous–Unemotional Traits* (ICU; 11 to 17 years (Frick, 2004)) is a 24-item self-report questionnaire. There are parent- and child-rated versions. A total score can be calculated. Higher scores suggest higher levels of CU traits.

**DBD and social competence:** The *Diagnostic System for Mental Disorders in Children and Adolescents* (DISYPS; 4 to 18 years; (Döpfner et al., 2017)) assesses diagnostic criteria for conduct problems according to ICD-10 and DSM-5 across 55 items. There are parent- and child-rated versions. A total score and six subtest scores (oppositional behavior, aggressive-dissocial behavior, limited prosocial emotions, disruptive affect regulation disorder & irritability, functional impairment, DBD score, and social competence) can be calculated. Higher scores suggest higher symptom levels.

Primary caregiver-rated

**Aggressive behavior, attention problems, physical complaints, depression, and anxiety**: The *Child Behavior Checklist* (*CBCL*; 6 to 18 years (Döpfner et al., 2014)) is a 119-item questionnaire for assessing emotional and behavioral problems in eight primary (anxious/depressed; withdrawn/depressed, physical complaints, social problems, thinking, sleep and repetitive problems, attention problems, rule-breaking behavior, aggressive behavior) and three secondary subscales: internal (anxious/depressed; withdrawn/depressed, physical complaints), external (rule-breaking behavior, aggressive behavior) and general problems (social problems, thinking, sleeping and repetitive problems, attention problems). Higher scores on the scales indicate behavior problems in this area.

**Parental warmth and parental strictness:** The *Parenting Style Inventory* (PSI, no years recommended (Satow, 2013)) assesses parenting behavior using 54 items. A total of six scale values—love, strictness, independence, religiosity, cooperation with a partner, and collaboration with a school—can be calculated. The study will focus on the warmth subscale (10 items; parenting characterized by love, appreciation, and recognition) and the strictness subscale (10 items; parenting characterized by control, rules, and punishment). Higher scores on these scales suggest that the parents are either stricter or warmer.

**Socio-economic status:** Following Lang and colleagues (Lang et al., 2022), a sum index is created based on the educational level of the mother and father (four categories for years in the education system: <9 [1], 9 [2], 10–12 [3] or 13 [4] years), the origin of the mother and father (two categories: international [0] or national [1]) and net monthly family income (six categories: less than 1000 EUR [1], 1000–2000 EUR [2], 2000–3000 EUR [3], 3000–4000 EUR [4], 4000–5000 EUR [5], more than 5000 EUR [6]). There is, therefore, a theoretical range of 3 to 16.

Child-rated

**Proactive aggressive behavior and reactive aggressive behavior**: The *Differential Aggression Questionnaire* (DAF, 10 to 16 years (Petermann & Beckers, 2014)) has three scales (proactive aggression, reactive aggression, and overall aggression) and 16 items. In this study, the scales for proactive and reactive aggression will be used. Higher scores indicate higher levels of aggression.

**Empathy**: The *Questionnaire on Resources in Childhood and Adolescence* (FRKJ; 8 to 16 years (Lohaus & Nussbeck, 2016)) uses 60 items to assess six personal (empathy and perspective-taking, self-efficacy, self-esteem, sense of coherence, optimism, self-control) and six social (parental emotional and social support, authoritative parenting style, peer group integration, school integration) resources of children and adolescents. Only the empathy subscale (6 items) is used in this study. Higher scores suggest higher levels of empathy.

**Emotion recognition**: The *Diagnostic and Therapeutic Procedure for Accessing Emotions in Children and Adolescents* (EMO-KJ, 5–16 years; (Kupper & Rohrmann, 2018)) offers a child-rated questionnaire (23 items) for emotion recognition (happy, sad, angry, anxious, shy, disgusted, proud, and ashamed). The emotion recognition scores are binary (yes/no). In this study, a sum score is used as an emotion recognition score.

**Traumatic event:** The *Children and Adolescent Trauma Screen 2* (CATS-2; 7–17 years (Sachser et al., 2022)) is a questionnaire used to assess criteria for post-traumatic stress disorder according to DSM-5. On the first page, 14 potentially traumatic events are recorded as yes (1) or no (0); on the second, clinical symptoms are rated from never (0) to almost always (3). In this study, the total number of affirmed potentially traumatic events is calculated, with a possible range from 0 to 14.

### 2.6. Statistical Analysis

All constructs are procedures that have been validated in Germany; the manualized procedure was adhered to. It is important to note that all scales, except those designed for DBD and social competence, are expressed as total scores. DBD and social competence were utilized as means.

**Research question 1:**

*Interrater reliability*

To ascertain interrater reliability, all CAPE interviews will be independently coded by a second rater in a double-blind (no information on questionnaire data and SPJ from the treating clinician) coding process. The secondary coder will either be a psychology student (master’s candidate), a trained child and adolescent psychotherapist, or a trained physician. We will use quadratically weighted Cohen’s κ to estimate interrater reliability.

*Convergent and divergent validity*

Pearson correlations are used to assess discriminative validity (empathy, emotion recognition, parental warmth, social competence) and convergent validity (proactive aggression, DBD, CU traits, aggressive behavior, parental strictness).

*Incremental validity*

Hierarchical regression analyses will be conducted to determine whether the dimensional CAPE score can serve as an incremental predictor of DBD, social competence, proactive aggressive behavior, empathy, emotion recognition, and the control variables of age and gender beyond the ICU.

*Group comparison of the specifier “with limited prosocial emotions”*

This study aims to investigate the hypothesis that children with or without CAPE LPE differ in levels of CU traits, DBD, and social competence, parental warmth/strictness, (reactive/proactive) aggressive behavior, empathy, and emotion recognition. To this end, an analysis of covariance (ANCOVA) will be performed. We will control for age, study site (waiting list, outpatient, daycare, or inpatient), traumatic event, anxiety (to account for primary and secondary CU traits), and sex in the ANCOVA models.

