In accordance with the study by Neo et al. (2023), the *κ* values will be interpreted using Altman’s (1991) guidelines: values ranging from 0.80 to 1.00 will be classified as indicating very good agreement, values ranging from 0.60 to 0.80 will be classified as indicating good agreement, values ranging from 0.40 to 0.60 will be classified as indicating moderate agreement, values ranging from 0.20 to 0.40 will be classified as indicating fair agreement, and values below 0.20 will be classified as indicating poor agreement. Effect sizes will be estimated using η^2^ (small = 0.01, medium = 0.06, and large = 0.14 (Cohen, 1988)). To correct for multiple testing, Alpha levels will be Bonferroni-Holm corrected.

Before conducting the ANCOVA, a comprehensive series of prerequisite checks will be conducted. These checks encompass the identification of potential outliers (±3 standard deviations), the assessment of linearity between covariate and dependent variables through scatter plots, the evaluation of homoscedasticity via residual plots, and the confirmation of the normal distribution of the disturbance variables through histograms of the standardized residuals and P-P plots. Independence of observations will be addressed through the study design. Multicollinearity is evaluated using variance inflation factors (VIFs). The assumption of homogeneity of regression slopes will be tested by examining the interaction between the grouping variable and the covariate.

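### The only interrater statistic named, quadratically weighted κ, does not measure agreement on the LPE yes/no decision; an unweighted κ for that decision should be added

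*Protocol article*

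**What the plan says.** Section 2.6 (Research question 1, Interrater reliability) has every CAPE interview coded a second time by a blinded rater and names one statistic: "We will use quadratically weighted Cohen’s κ to estimate interrater reliability". It does not name the rating on which κ is computed.

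Section 2.5 (CAPE) scores each of four CU traits 0, 1 or 2, where 2 is 'highly descriptive'. The diagnostic rule is: "If there are two CU traits rated as ‘highly descriptive’, LPE diagnosis is assigned". The same section adds: "For data analysis, the dimensional and dichotomous (LPE yes/no) score will be used".

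Section 2.6 (Research question 2, Defining groups) uses a second rule on the same ratings: "Patients with ‘highly descriptive’ in at least one CU Trait on the CAPE interview will be separated into two groups".

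Hypothesis 1 in section 1.3 reads: "The CAPE interviews are expected to demonstrate moderate to very good interrater reliability". The closing part of section 2.6 interprets κ in fixed bands, among them "values ranging from 0.60 to 0.80 will be classified as indicating good agreement" and "values ranging from 0.20 to 0.40 will be classified as indicating fair agreement". Section 1.4 anticipates κ between 0.50 and 0.90.

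**The concern.** Both classifications treat a rating of 1 exactly like a rating of 0; only 2 versus lower counts. Quadratic weighting treats a 1-versus-2 split as a minor disagreement. The named coefficient is thus least sensitive, among real disagreements, to the ones that can change a child's classification, and it gives the same credit to 0-versus-1 splits, which change nothing.

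Research question 1 asks whether LPE can be validly diagnosed, and LPE yes/no is the grouping variable for the comparisons in hypotheses 6 and 7. If the plan is followed in its ordinal reading, hypothesis 1 would be judged on a coefficient that leaves the reliability of that grouping unestimated. Even a κ on LPE yes/no alone would not cover the separate one-trait rule for research question 2.

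**Working it through.** The article derives no figure for κ beyond the anticipated range, so there is no calculation to reproduce.

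**Weights.** For k ordered categories the agreement weight is w = 1 − (i − j)²/(k − 1)².
- Trait rating, k = 3: 1.00 for agreement, 1 − 1/4 = 0.75 for adjacent ratings, 0 for 0 versus 2.
- Dimensional score, taken here as a 0-8 sum of four traits (an assumption; the article does not define it), k = 9: a one-point difference earns 1 − 1/64 = 0.984.
- LPE yes/no, k = 2: weights 1 and 0, so weighted and unweighted κ coincide.

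**Same coefficient, different decisions.** Weighted κ = 1 − Σ d·p(observed) / Σ d·p(expected), with d = 1 − w. The tables are constructed, since the article gives no rating distribution.

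*All disagreement at 1/2* (rows 40,0,0 / 0,15,15 / 0,15,15; margins 40/30/30):
- Observed: 0.25 × 0.30 = 0.075.
- Expected: 0.25 × (2×0.4×0.3 + 2×0.3×0.3) + 2×0.4×0.3 = 0.105 + 0.240 = 0.345.
- Weighted κ = 1 − 0.075/0.345 = 0.783 ('good').
- For 2 versus lower: agreement 0.70, chance 0.7² + 0.3² = 0.58, κ = 0.12/0.42 = 0.286 ('fair').

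*All disagreement at 0/1* (rows 15,15,0 / 15,15,0 / 0,0,40; margins 30/30/40):
- Observed 0.075; expected 0.25 × (2×0.3×0.3 + 2×0.3×0.4) + 2×0.3×0.4 = 0.345; weighted κ again 0.783.
- For 2 versus lower: no disagreement, κ = 1.00.

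A weighted κ of 0.78 is therefore compatible with fair or with perfect agreement on the cut that matters.

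*Intermediate table* (rows 36,4,0 / 4,16,10 / 0,10,20): weighted κ = 1 − 0.07/0.345 = 0.797; for 2 versus lower, (0.80 − 0.58)/0.42 = 0.524.

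**Symmetric rater error.** Assumptions: four traits with normal latent scores, rating shares 40/30/30, latent correlation between traits 0.3 to 0.7, 400,000 simulated cases. Simulated LPE prevalence was about 0.35, between the 21.6% and 60% that section 1.4 cites but below the expected half. Ranges run over the trait correlation.

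| Rater correlation | Trait weighted κ | One trait, 2 vs lower | LPE yes/no | At least one trait at 2 |
|---|---|---|---|---|
| 0.7 | 0.59 | 0.48 | 0.49-0.59 | 0.45-0.55 |
| 0.8 | 0.69 | 0.58 | 0.57-0.67 | 0.55-0.63 |
| 0.9 | 0.80 | 0.70 | 0.68-0.75 | 0.67-0.73 |

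At the middle trait correlation (0.5), trait-level weighted κ exceeds LPE κ by 0.04 to 0.08 and entry-rule κ by 0.08 to 0.10. Over all settings the differences run from −0.01 to 0.14. If κ were computed on the 0-8 sum instead, it would be 0.80 to 0.87 at rater correlation 0.8, about 0.2 above LPE κ. Part of that gap arises because a sum of four ratings is more reliable than one rating.

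**Disagreement only at 1/2, four traits.** Trait-level weighted κ stays at 0.78, while LPE κ is 0.29 to 0.37 and entry-rule κ 0.34 to 0.55.

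**The case against.** The strongest reply is that the article does not fix which rating κ applies to. Section 2.1 describes the clinician's evaluation as LPE yes/no, and on that rating the weighting has no effect. A condensed article may leave the choice to a fuller document. This stands in part: if κ is meant for LPE yes/no, the main problem disappears. But quadratic weights have no function for two categories, so naming them points to an ordinal rating. The point concerns a stated choice, not only an omitted detail.

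Second, quadratically weighted κ is a standard choice for ordered ratings, and the plan relies on the dimensional CAPE score for incremental validity. This stands fully. A reader might infer that weighted κ is the wrong statistic and should be replaced; the documents do not support that.

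Third, a reader might infer that the plan will report good reliability for an unreliable diagnosis, with κ overstated by 0.45 or more. The documents give no ground for expecting that. A gap of that size can be built, for example with 84 ratings in rows 36,3,0 / 3,6,12 / 0,12,12: weighted κ 0.75 against 0.30 for 2 versus lower. But among the 42 ratings that both raters place at 1 or 2, agreement is 18/42 = 0.43 against 0.51 by chance (κ about −0.17). Such raters do worse than chance at that boundary while separating 0 from the rest almost perfectly. The 40/30/30 table likewise needs raters exactly at chance there. Nothing suggests this of the trained raters in section 2.5.

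Fourth, research question 2 is labelled exploratory, and section 1.4 openly warns that coding from written notes may lower reliability. Both are true and limit the stakes. Neither supplies an estimate for the diagnosis.

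**Conclusion.** The point holds in a limited form. In its natural ordinal reading, the named coefficient gives 75% or more credit to a 1-versus-2 split, although LPE and entry to research question 2 turn only on 2 versus lower. It does not show agreement on the diagnosis and may lie on either side of it. For trait ratings under symmetric error the gap is typically about 0.05 to 0.1, enough to move a result by one band in some cases. In the middle case (rater correlation 0.8), every value stays moderate or good, so hypothesis 1 would still be met. Larger gaps need disagreement concentrated at one boundary. All sizes rest on assumed rating distributions and error patterns. The exact parts are the weights and the fact that one weighted κ is compatible with very different agreement on the decision.

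**What to change.** Make three changes in section 2.6:

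- State that quadratically weighted κ applies to the 0-2 trait ratings and supports the dimensional use of the CAPE, and keep it for that purpose.
- Add unweighted κ with a 95% CI for LPE yes/no, named as the reliability estimate that supports the diagnostic claim of research question 1.
- Report as supplements κ for each trait at 'highly descriptive' versus lower, and κ for the at-least-one-trait entry rule of research question 2.

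All interviews are to be double-coded anyway, so no new data are needed. The cost is a few more coefficients to report, and a κ for the diagnosis that may be somewhat lower than the weighted one.
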